### Interventions

#### GAE/Sham Procedure

Participants will be randomly allocated (1:1) to GAE or sham treatment using a computational generator created using code in Excel. The generator is maintained on a password protected research server. On the procedure day, an unblinded trained radiographer will inform the staff performing the study procedure of the participant’s allocation. At the 1-month and 6-month visits, participants will be asked which group they believed they were allocated to in order to assess accuracy of blinding. At 6 months post-randomisation, the participants and the study team will be unblinded. 6 months was chosen for unblinding as we know from prior studies that the median time for participants to reach maximum benefit from GAE is at least 3-months [10]. More importantly, we need a time period long enough to formally capture the placebo effect, whilst considering a time reasonable for participants to remain in the sham arm to maximise study recruitment, and minimise drop out.

GAE will be performed using 100-micron Embozene™ embolisation particles and following previously described methods for GAE [6]. The pathological embolisation target of the genicular arteries that supply the diseased portion of the knee is determined by patient symptoms and classical hyperaemic blush on angiography. All genicular arteries pertaining to the patients pain/synovitis demonstrated on preceeding contrast-enhanced MRI will be interrogated. Cone-beam CT (Allura FD20, Philips, Amsterdam) with contrast (6 ml of 100% contrast, 0.3 ml/s, 6 s delay) will be performed to confirm the hyperaemic target. A sports ice pack will be placed on the skin surface of the knee corresponding to the area to be embolised, minimising non-target embolisation to cutaneous branches by temporary vasoconstriction. The vessels will be embolised with 0.1–0.3 ml of embolic agent at a time to prune the abnormal vessels. The sham procedure will be identical to the GAE procedure, except that 2 ml heparinised 0.9% saline, instead of the embolic agent, will be slowly injected. Participants will be monitored for 4 h post-procedure.

Follow-up data will be collected at 1, 3, 6, 12, and 24 months post-randomisation (Table 2).

**Table 2 Tab2:** Participant timeline

Timepoint	Study period														
	Enrolment	Allocation and treatment		Post-allocation						Post-treatment crossover to GAE after unblinding					

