		Pre-Tx	Tx	1 week	1 mos^a^	3 mos^a^	6 mos^b^	12 mos^b^	24 mos^b^	1 week	1 mos^a^	3 mos^a^	6 mos^b^	12 mos^b^	18 mos^b^
*Enrolment*															
Informed Consent	X														
Demographics, medical history	X														
*Interventions*															
Randomisation		X													
GAE			X												
Sham			X												
Crossover to GAE							X								
*Assessments*															
Eligibility confirmation	X														
KOOS, VAS	X				X	X	X	X	X		X	X	X	X	X
Analgesia questionnaire	X				X	X	X	X	X		X	X	X	X	X
EQ-5D-3L	X						X	X	X				X	X	X
Knee MRI		X					X	X					X	X	
Neuroscience assessments		X													
Pre-existing conditions		X													
PROM				X						X					
Opinion of intervention					X		X								
AE check					X	X	X	X	X	X	X	X	X	X	X
Study completion									X						X
Durability of GAE									X						X

^a^** ± **5 days

^b^** ± **10 days

At 6 months post-randomisation, after unblinding, sham participants will have the option to undergo the GAE procedure (crossover). Participants electing to cross over will have 18 months of post-GAE follow-up.

Subjects may use analgesia, as indicated, throughout the study. Analgesia use will be collected from a participant self-reported analgesia questionnaire.

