### Secondary Outcomes with Descriptive Statistics

*OA symptom relief* Proportion of subjects reporting ≥ 10-point improvement in KOOS scores for each of the 5 KOOS subscales at 6 months post-randomisation*Safety* The proportion of subjects experiencing relevant adverse events that are possibly, probably, or definitely related to treatment received, GAE or Sham, from randomization through 6 months post randomization will be summarized by severity and compared between GAE and sham arms [15].*Synovial hypertrophy and neo-vascularisation* Whole-Organ Magnetic Resonance Imaging Score (WORMS) [14] at 6 months post-randomisation*Neural and behavioural indicators of predisposition to central facilitation of pain* Three assessments quantifying (1) sensory pain profiles, (2) psychological profiles, (3) individual differences in neurochemistry and functional connectivity, with psychological profile quantified and calibrated for pain sensitivity and modulatory ability at 6 months post-randomisation*Quality of life* Pre- and post-intervention EuroQoL-5D (EQ-5D-3L) for GAE versus non-crossover sham participants at 6 months post-randomisation*Patient-reported acceptability of study procedure* Questionnaire 1 week after GAE

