### Exploratory Outcomes

*Analgesia intake reduction from baseline* Analgesia questionnaire through 6 months post-randomisation*Durability* Time from GAE procedure to next invasive intervention for knee OA*Comparative cost-effectiveness* Payer-perspective health economic analysis of GAE versus standard of care, including integration of EQ-5D-3L-based quality-adjusted life-years, and durability.*GAE group outcomes* KOOS, EQ-5D-3L, analgesia questionnaire, and VAS at 1, 3, 6, 12, and 24 months post-randomisation*PROMs for sham treatment without crossover versus GAE* 12 and 24 months post-randomisation*Imaging changes GAE versus sham* WORMS at 12 and 24 months post-randomisation*Sham group outcomes* KOOS, VAS, and analgesia questionnaire diary at 1, 3, 6, 12 (crossover), and 18 months (crossover); EQ-5D-3L at 6, 12 (crossover), and 18 months (crossover); MRI at 6 and 12 months (crossover) post-randomisation.

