### Sample Size

Alongside a sham surgery placebo arm, a high-quality systematic review of surgical RCTs was used as a suitable benchmark to inform the sample size and power calculation [16, 17]. With a 0–100 scale for the primary endpoint of KOOS_4_, assuming a 1:1 randomisation, a mean difference of 6.4 (i.e. effect size) between GAE and sham treatments, a common standard deviation of 10 (a Cohen’s D of 0.64), an alpha error of 2-sided 0.05, and a power of 0.85, the 2-arm total sample size requirement is 88 subjects (44 each arm) by Normal approximation. Allowing for a participant dropout rate of 20%, the enrolment goal is 110 participants, approximately 55 in each study arm. Study activities (Table 2) will take place at a single academic centre in the UK.

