### Statistics

#### Endpoints

All efficacy analyses will be performed on the intention-to-treat population (all randomised subjects).

Change of KOOS4 (mean of pain, symptoms, activities of daily living, and quality of life subscores) will be compared between GAE and sham treatment arms in an ANCOVA model (vs. treatment arm indicator and baseline KOOS4 score). A secondary ANCOVA model will further include pain medication taken through 6 months.

The proportion of subjects achieving the MCID (10 points) will be compared between the sham treatment and GAE arms by Fisher’s exact test for all 5 KOOS subscales.

Subjects’ 6-month VAS will be compared between GAE and sham treatment arms in an ANCOVA model (vs. treatment arm and baseline pain score). Should the VAS be generally low, score will be dichotomised to with (> 0) or without pain (= 0), and a logistic regression analysis will be performed.

All 5 subscales of the KOOS questionnaire will be analysed at 6 months follow-up. Each sub-scale will be compared between the GAE and sham arms in an ANCOVA model (vs. treatment arm indicator and the baseline sub-scale score). An additional analysis will further include investigational site in the model.

All remaining endpoints will be descriptive, and formal hypothesis testing will not be performed. Continuous data will be reported as mean, standard deviations, median, minimum, and maximum. Categorical data will be summarised as frequency and proportions.

The proportions of subjects experiencing relevant adverse events that are possibly, probably, or definitely related to treatment received, GAE or sham treatment, from randomisation through 6 months post-randomisation will be summarised by severity and compared between GAE and sham arms.

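### The 6-month EQ-5D-3L comparison is limited to non-crossover sham participants, although crossover is not offered until 6 months; the qualifier should be deleted

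*Protocol article*

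**What the plan says.** Under Secondary Outcomes with Descriptive Statistics, the quality-of-life item is EQ-5D-3L before and after intervention, "for GAE versus non-crossover sham participants at 6 months post-randomisation".

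The GAE/Sham Procedure section fixes the timing: "At 6 months post-randomisation, the participants and the study team will be unblinded", and then "At 6 months post-randomisation, after unblinding, sham participants will have the option to undergo the GAE procedure (crossover"). Table 2 lists EQ-5D-3L in the 6-month column of the post-allocation block. It gives those who cross over a separate block with its own visits.

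The Endpoints section sets the analysis population: "All efficacy analyses will be performed on the intention-to-treat population (all randomised subjects"). It also gives the status of outcomes outside the tested set: "All remaining endpoints will be descriptive, and formal hypothesis testing will not be performed".

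Exploratory Outcomes has a similar restriction, "PROMs for sham treatment without crossover versus GAE", but at 12 and 24 months.

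**The concern.** A restriction to participants who did not cross over can be motivated once some sham participants have received GAE. At 6 months none has, so both randomised arms are still intact.

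Whether a sham participant counts as non-crossover is settled only at or after the 6-month assessment, once allocation is known, and the state being measured plausibly influences the choice. Nobody in the GAE arm faces the same choice. Taken literally, the definition compares a whole randomised arm with a self-selected part of the other.

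At stake is the between-arm EQ-5D-3L contrast at 6 months. If sham participants who opt for GAE tend to be those doing worse, those who remain look better than the randomised sham arm and the contrast leans against GAE. Precision falls as well, because sham data are discarded.

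**Working it through.** **Timing and population, place by place**

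| Place in the article | Time | Sham participants compared |
|---|---|---|
| Primary Outcomes (KOOS4) | 6 months | no crossover restriction |
| Secondary outcomes with hypothesis testing (clinical success, VAS) | 6 months | no crossover restriction |
| Descriptive secondaries: KOOS subscales, WORMS | 6 months | no crossover restriction |
| Descriptive secondary: EQ-5D-3L | 6 months | non-crossover only |
| Exploratory PROMs | 12 and 24 months | without crossover only |
| Endpoints, population rule | all efficacy analyses | all randomised |

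EQ-5D-3L is the only 6-month outcome with the restriction. The other use of it falls after crossover has become possible.

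**The plan's own figures**

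The Sample Size section assumes "a mean difference of 6.4 (i.e. effect size) between GAE and sham treatments" and "a common standard deviation of 10", two-sided alpha 0.05 and power 0.85. By the Normal approximation:

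n per arm = 2 × (1.960 + 1.036)² × (10/6.4)² = 43.8, rounded up to 44, so 88 in total. With 20% dropout, 88/0.80 = 110.

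The stated figures reproduce, and this point does not affect them. They supply 44 evaluable participants per arm for the illustration. The article gives no design figures for EQ-5D-3L.

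**Illustration of the literal reading**

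Two inputs are assumptions, because the article gives neither: the fraction f of sham participants who cross over, and the correlation rho between the tendency to cross over and poorer 6-month EQ-5D-3L. Let p = 1 − f be the share retained, and let the decision follow a latent normal variable. Then:

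- upward shift of the retained sham mean, in SD = rho × φ(z)/p, with z = Φ⁻¹(f);
- SE of the difference, in SD = √(1/44 + 1/(44p)), against √(2/44) = 0.213 with all sham participants.

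| f | φ(z)/p | Shift, rho = 0.3 | Shift, rho = 0.5 | Sham kept of 44 | SE (ratio to 0.213) |
|---|---|---|---|---|---|
| 0.30 | 0.348/0.70 = 0.497 | 0.15 | 0.25 | about 31 | 0.235 (1.10) |
| 0.50 | 0.399/0.50 = 0.798 | 0.24 | 0.40 | 22 | 0.261 (1.22) |
| 0.70 | 0.348/0.30 = 1.159 | 0.35 | 0.58 | about 13 | 0.314 (1.47) |

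The GAE mean is unchanged, so the contrast moves against GAE by the shift shown. With no true difference it would read −0.15 to −0.58 SD. At rho = 0 the shift is zero; a negative rho would reverse its sign. The SE column takes the SD of the retained sham participants as unchanged, a simplification.

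**The case against.** **A harmless reading exists.** Table 2 has two 6-month columns with EQ-5D-3L, one after randomisation and one after crossover GAE. The qualifier may only have been meant to separate the first from the second. At 6 months after randomisation nobody has crossed over, so on that reading the set is the whole sham arm and nobody is dropped. The all-randomised rule supports it. This objection stands as far as intent goes: a reader might infer that the plan definitely discards the least satisfied sham participants and biases EQ-5D-3L towards no benefit, but that is one reading joined to an assumption about behaviour. It does not rescue the wording. Exploratory Outcomes uses an equivalent phrase for a real subset, and an analyst who follows the item literally would drop participants.

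**Quality of life is compared elsewhere.** A reader might take this as the only 6-month quality-of-life contrast. It is not. The KOOS quality-of-life subscale is part of KOOS4, and the Endpoints section compares all five subscales between arms at 6 months with no crossover restriction. Exploratory Outcomes also lists 6-month EQ-5D-3L for the GAE group and for the sham group, with only the later sham entries tagged as crossover. Full-arm summaries are therefore planned, and the data are not lost.

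**Carry-over into the QALYs is not stated.** The exploratory cost-effectiveness item uses EQ-5D-3L-based QALYs, but the article does not say that they rest on the restricted set.

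**The outcome is descriptive.** No hypothesis test depends on it. That lowers the severity, but a descriptive contrast can still mislead if its comparator is self-selected.

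**The magnitude is assumed.** This is correct. The planned 0.64 SD (6.4/10) belongs to KOOS4 and is not a benchmark for EQ-5D-3L.

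**Conclusion.** The concern holds as a defect in the stated comparison set, of minor to moderate severity. At 6 months the qualifier removes no contamination. Read literally, it conditions one arm on a decision made at or after the assessment and conflicts with the all-randomised rule.

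That the contrast would understate GAE rests on the expectation that those who cross over are doing worse at 6 months, which the article neither states nor contradicts. Under the assumed ranges (30% to 70% crossover, rho 0.3 to 0.5, 44 evaluable per arm) the shift is 0.15 to 0.58 SD and the SE rises by a factor of 1.10 to 1.47. These are illustrations, not estimates. Under the harmless reading there is neither a shift nor a loss of precision.

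The documents do not support treating this as a threat to the trial's conclusions: the primary outcome, the tested secondaries and the sample size are untouched.

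**What to change.** In the quality-of-life item under Secondary Outcomes with Descriptive Statistics, delete *non-crossover* and define the comparison as 6-month EQ-5D-3L, GAE versus sham, in all randomised participants as randomised. State that the value used is the one collected before unblinding and crossover. Keep the restricted comparison only for the 12- and 24-month exploratory PROM item.

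The edit is the same under either reading. It needs no new data, visits or change in sample size. It is best made before the analysis, so that neither crossover uptake nor results can influence the choice.

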### Exploratory Outcomes

*Analgesia intake reduction from baseline* Analgesia questionnaire through 6 months post-randomisation*Durability* Time from GAE procedure to next invasive intervention for knee OA*Comparative cost-effectiveness* Payer-perspective health economic analysis of GAE versus standard of care, including integration of EQ-5D-3L-based quality-adjusted life-years, and durability.*GAE group outcomes* KOOS, EQ-5D-3L, analgesia questionnaire, and VAS at 1, 3, 6, 12, and 24 months post-randomisation*PROMs for sham treatment without crossover versus GAE* 12 and 24 months post-randomisation*Imaging changes GAE versus sham* WORMS at 12 and 24 months post-randomisation*Sham group outcomes* KOOS, VAS, and analgesia questionnaire diary at 1, 3, 6, 12 (crossover), and 18 months (crossover); EQ-5D-3L at 6, 12 (crossover), and 18 months (crossover); MRI at 6 and 12 months (crossover) post-randomisation.

### Sample Size

Alongside a sham surgery placebo arm, a high-quality systematic review of surgical RCTs was used as a suitable benchmark to inform the sample size and power calculation [16, 17]. With a 0–100 scale for the primary endpoint of KOOS_4_, assuming a 1:1 randomisation, a mean difference of 6.4 (i.e. effect size) between GAE and sham treatments, a common standard deviation of 10 (a Cohen’s D of 0.64), an alpha error of 2-sided 0.05, and a power of 0.85, the 2-arm total sample size requirement is 88 subjects (44 each arm) by Normal approximation. Allowing for a participant dropout rate of 20%, the enrolment goal is 110 participants, approximately 55 in each study arm. Study activities (Table 2) will take place at a single academic centre in the UK.

### Safety

The investigator will oversee study safety, including documenting and assessing all of participants’ AEs, regardless of severity or attribution. The number and type of serious AEs (SAEs) will be evaluated regularly, and procedure-related SAEs will also trigger assessment of whether any changes are needed to the protocol, patient informed consent, or other study documents or procedures.

After 5 subjects underwent GAE, GAE, and sham procedures stopped. A short safety and performance report was submitted to the MHRA for review. The MHRA made the determination that the study could resume based on this initial analysis.

### Statistics

#### Endpoints

All efficacy analyses will be performed on the intention-to-treat population (all randomised subjects).

Change of KOOS4 (mean of pain, symptoms, activities of daily living, and quality of life subscores) will be compared between GAE and sham treatment arms in an ANCOVA model (vs. treatment arm indicator and baseline KOOS4 score). A secondary ANCOVA model will further include pain medication taken through 6 months.

The proportion of subjects achieving the MCID (10 points) will be compared between the sham treatment and GAE arms by Fisher’s exact test for all 5 KOOS subscales.

Subjects’ 6-month VAS will be compared between GAE and sham treatment arms in an ANCOVA model (vs. treatment arm and baseline pain score). Should the VAS be generally low, score will be dichotomised to with (> 0) or without pain (= 0), and a logistic regression analysis will be performed.

All 5 subscales of the KOOS questionnaire will be analysed at 6 months follow-up. Each sub-scale will be compared between the GAE and sham arms in an ANCOVA model (vs. treatment arm indicator and the baseline sub-scale score). An additional analysis will further include investigational site in the model.

All remaining endpoints will be descriptive, and formal hypothesis testing will not be performed. Continuous data will be reported as mean, standard deviations, median, minimum, and maximum. Categorical data will be summarised as frequency and proportions.

The proportions of subjects experiencing relevant adverse events that are possibly, probably, or definitely related to treatment received, GAE or sham treatment, from randomisation through 6 months post-randomisation will be summarised by severity and compared between GAE and sham arms.

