#### Pain, Function, and Quality of Life Assessment

Knee Injury and Osteoarthritis Outcome Score (KOOS) is a validated questionnaire used within the orthopaedic literature to assess the effect of interventions on the perceived severity of knee OA [12] and has previously been reported in the GAE literature [5, 6]. KOOS is intended to be used over short- and long-term time intervals, to assess changes from week to week induced by treatment (medication, operation, physical therapy) or over years following a primary injury or OA. KOOS is responsive to change following non-surgical and surgical interventions (Online Appendix A). The primary outcome measure for the current study is improvement in the 4 Knee Injury and OA Outcome Score subscales (KOOS_4_), covering pain, symptoms, activities of daily living, and quality of life at 6 months in patients with mild to moderate knee OA. Sports and recreation were the most inconsistently reported measure from Genesis, hence its exclusion [6]. Total KOOS will be analysed as a secondary endpoint. The Minimum Clinically Important Difference (MCID) will be used to define clinical success. A 10-point increase in KOOS scores will be used to define the MCID based on the work by Roos [6, 12]. The proportion of participants achieving the MCID at 6 months will be compared between the GAE and sham treatment for all 5 KOOS subscales. In addition to the quality of life assessment from the KOOS questionnaire, the EuroQoL-5D (EQ-5D-3L) will be completed.

A visual analogue scale (0–100) will also be used to assess pain in the affected knee. This will be performed at baseline, with participants with a VAS < 50 excluded.

Analgesia use will not be controlled throughout the study. Participants will be asked if they are taking analgesia specific to their knee pain at follow-up, enabling longitudinal trends in analgesia use to be compared to treatment response following GAE or the sham procedures.

Pain, function, analgesia, and quality of life assessment data will be prospectively collected using a purposely designed Electronic Data Capture System (EDC).

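### The secondary KOOS4 model adjusts for on-study pain medication, so if GAE changes analgesic use its arm coefficient does not estimate the treatment effect

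*Protocol article*

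**What the plan says.** In the protocol article, under Statistics (Endpoints), change in KOOS4 is compared between arms "in an ANCOVA model (vs. treatment arm indicator and baseline KOOS4 score"). The next sentence adds: "A secondary ANCOVA model will further include pain medication taken through 6 months". The population is also fixed there: "All efficacy analyses will be performed on the intention-to-treat population (all randomised subjects").

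Three other places describe analgesia:

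- **GAE/Sham Procedure:** "Subjects may use analgesia, as indicated, throughout the study".
- **Pain, Function, and Quality of Life Assessment:** "Analgesia use will not be controlled throughout the study". Use is recorded at follow-up, "enabling longitudinal trends in analgesia use to be compared to treatment response following GAE or the sham procedures".
- **Exploratory Outcomes:** "Analgesia intake reduction from baseline", measured by "Analgesia questionnaire through 6 months post-randomisation".

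Table 2 schedules the analgesia questionnaire at enrolment and again at 1, 3 and 6 months and later.

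**The concern.** The same variable, over the same window, serves as an outcome and as an adjustment covariate. Analgesia is taken according to need. If GAE relieves pain, as the trial hypothesises, need and therefore use should differ between arms.

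Conditioning on such a variable does two things. It removes any part of the GAE effect that runs through analgesia. It also makes arm and unmeasured pain severity dependent among participants with equal use: a sham participant with low intake is probably a milder case than a GAE participant with the same intake. The arm coefficient then mixes the treatment effect with a severity imbalance that randomisation had excluded.

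The article does not say what effect this model is meant to estimate and sets no limit on its interpretation. A gap between the two models could be read as evidence that GAE works less well, or better, once medication is taken into account. Neither reading would be justified.

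**Working it through.** **The plan's own figure.** Under Sample Size the inputs are a difference of 6.4, SD 10, two-sided alpha 0.05, power 0.85, 1:1 allocation and 20% dropout.

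- Per arm: 2 × (1.960 + 1.036)² × 10² / 6.4² = 43.8, rounded up to 44, so 88 in total.
- Enrolment: 88 / 0.80 = 110.

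Both stated figures are reproduced. They rest on the unadjusted comparison of arms and do not involve analgesia.

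**Effect of the covariate.** The article gives no figure for the effect of GAE on analgesia or of analgesia on KOOS4. The following quantities are therefore assumptions:

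- a: change in analgesic use caused by GAE, in SD units (0, −0.2, −0.5);
- b: effect of analgesia on KOOS4, in points per SD of use (0 or 3);
- g: loading of unmeasured severity on analgesic use (0 or 0.5);
- h: KOOS4 points lost per SD of severity (0 or 5).

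The total effect is held at 6.4 and the within-arm SD at 10. Baseline KOOS4 is left out of both models for simplicity, so severity here means what baseline KOOS4 does not capture.

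Within arm, the slope of KOOS4 change on analgesic use is b − gh. The coefficients are:

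- arm coefficient without the covariate: 6.4;
- arm coefficient with the covariate: 6.4 − a(b − gh);
- true direct effect: 6.4 − ab.

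| a | Analgesia helps only (b = 3, g = h = 0) | Tracks severity only (b = 0, g = 0.5, h = 5) | Both (b = 3, g = 0.5, h = 5) |
|---|---|---|---|
| 0 | 6.4 | 6.4 | 6.4 |
| −0.2 | 6.4 + 0.2 × 3 = 7.0 | 6.4 − 0.2 × 2.5 = 5.9 | 6.4 + 0.2 × 0.5 = 6.5 |
| −0.5 | 6.4 + 0.5 × 3 = 7.9 | 6.4 − 0.5 × 2.5 = 5.15 | 6.4 + 0.5 × 0.5 = 6.65 |

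A simulation with 400,000 participants per scenario agrees: in the last row it gave 7.92, 5.18 and 6.66. Without the covariate it returned 6.36 to 6.45 in every scenario.

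**Is it at least a direct effect?** Only when no unmeasured cause is shared. In the last row the direct effect is 7.9, 6.4 and 7.9 across the three columns, against adjusted values of 7.9, 5.15 and 6.65. The second and third columns miss it.

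**Power of the secondary test in the lowest case.**

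- Residual SD: √(100 − 2.5²) = 9.68.
- Squared correlation of arm with analgesia: 0.0625 / 1.0625 = 0.059.
- Standard error: 9.68 × √[(2/44) / 0.941] = 2.13.
- Power: Φ(5.15 / 2.13 − 1.96) = Φ(0.46), about 0.68, against 0.85 for the unadjusted comparison.

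**The case against.** **The primary analysis is clean.** It contains only arm and baseline KOOS4, in all randomised participants. A reader might infer that the trial's main result is compromised. It is not: the primary estimate, its type I error and the sample size do not depend on the secondary model. This stands and limits the severity.

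**The article never says that GAE changes analgesia.** It lists a reduction as an exploratory outcome, which is an open question. This stands too, so the bias is conditional. Still, the model is safe for the total effect only if GAE leaves use unchanged, if use is unrelated to KOOS4 within arms, or if opposing mechanisms happen to cancel. A trial built on the hypothesis of symptom relief should not rely on any of these.

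**Adjustment need not weaken the effect.** A reader might infer that the covariate must dilute a real benefit. That follows if intake is purely a consequence of the outcome, a structure that can only attenuate. If analgesia itself improves scores, the estimate moves up, and with both mechanisms acting the net shift can be small. The article supports no single direction.

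**The model does not carry the supporting evidence alone.** The article also plans baseline-adjusted ANCOVAs of all five KOOS subscales, the comparison of proportions reaching the 10-point MCID, and an analysis of total KOOS. None is described as adjusting for medication, and a reader should not infer that support for KOOS4 rests on this model.

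**Coding of the covariate may be left to an analysis plan.** That is fair, and no complaint is made about it. But no coding of medication use up to month 6 makes it a pre-randomisation variable.

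**Conclusion.** The point holds as a moderate, should-fix comment on a secondary model. If GAE changes analgesic use, the arm coefficient is in general biased for the total intention-to-treat effect. It is not a valid direct effect either where unmeasured severity influences both analgesia and KOOS4, which is to be expected when analgesia is taken according to need.

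Under the assumed range the adjusted estimate runs from about 5.2 to 7.9 around a true 6.4, a bias of about −1.2 to +1.5 points, and the bias is zero if use does not change. These sizes rest on a linear model and on assumed values of a, b, g and h. They show what could happen and do not predict it. What does not depend on them is that the article fixes, as a covariate for its primary endpoint, a post-randomisation variable that it also treats as an outcome.

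**What to change.** In the Endpoints section, replace on-study pain medication in the secondary ANCOVA with analgesic use at baseline. Being measured before randomisation, it leaves the arm coefficient as an estimate of the total effect. Keep post-baseline analgesic use as the exploratory outcome it already is, reported by arm.

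If the sponsor wishes to keep the on-study medication model, add a statement that it is exploratory and does not estimate the treatment effect.

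The cost is one sentence in the protocol and the matching line in any analysis plan. Table 2 already schedules the questionnaire at enrolment, so no new data are needed, and the sample size of 88 evaluable and 110 enrolled does not change.

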### Secondary Outcomes with Hypothesis Testing

Clinical success: Proportion of subjects reporting ≥ 10-point improvement in KOOS scores, where a 10-point change from baseline is defined as the minimum clinically important difference (MCID) at 6 months post-randomisation.Pain relief: VAS change through 6 months post-randomisation.

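### The 10-point responder proportions are tested by an unadjusted Fisher's exact test, which gives up power that a baseline-adjusted analysis would keep

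*Protocol article*

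**What the plan says.** - **Outcome.** Under Secondary Outcomes with Hypothesis Testing, clinical success at 6 months is "Proportion of subjects reporting ≥ 10-point improvement in KOOS scores, where a 10-point change from baseline is defined as the minimum clinically important difference". The entry does not say which KOOS score is meant.
- **Test.** The Endpoints part of the Statistics section says the proportion achieving the MCID will be "compared between the sham treatment and GAE arms by Fisher’s exact test for all 5 KOOS subscales". No covariate and no adjusted supporting analysis is given.
- **Tier of the subscale proportions.** The same 10-point proportions for the five subscales are listed under Secondary Outcomes with Descriptive Statistics. The Endpoints text names no separate test for clinical success.
- **Use of baseline elsewhere in Endpoints.** Change in KOOS4 is compared "in an ANCOVA model (vs. treatment arm indicator and baseline KOOS4 score"). Each subscale is compared in an "ANCOVA model (vs. treatment arm indicator and the baseline sub-scale score"). VAS is compared in an "ANCOVA model (vs. treatment arm and baseline pain score"), that is, adjusted for baseline pain and not for KOOS.
- **Data.** Table 2 schedules KOOS at enrolment.
- **Planning inputs.** Sample Size assumes "a mean difference of 6.4 (i.e. effect size) between GAE and sham treatments" on KOOS4 and "a common standard deviation of 10 (a Cohen’s D of 0.64"), with 44 evaluable per arm. It does not say whether the SD is that of the change or of the score, and it gives no power for the responder outcome.

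**The concern.** Responder status is a cut of the change from baseline. When baseline and follow-up scores are imperfectly correlated, change is negatively correlated with baseline, so the baseline score predicts who responds. The plan uses that information for the continuous KOOS outcomes and drops it for the proportions. Fisher's test is also conservative at this sample size, so part of the allowed 5% error goes unused.

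Clinical success is one of only two outcomes in the hypothesis-tested secondary tier. If its power is little more than one half when the primary has 85%, a real effect could be shown on KOOS4 and missed on clinical success, partly because of the test chosen.

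**Working it through.** **1. The plan's own figure.** Inputs from Sample Size: difference 6.4, SD 10, two-sided alpha 0.05, power 0.85.

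n per arm = 2 × (1.960 + 1.036)² × 10² / 6.4² = 43.8, rounded up to 44, so 88 in total. 88 / 0.80 = 110 enrolled. Power at 44 per arm is 85.1%. The stated figures reproduce.

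**2. Responder rates implied by those inputs.** Assumptions: change is normal with SD 10. The sham mean change m is not in the document, so a range is used.

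P(response, sham) = Φ((m − 10)/10); P(response, GAE) = Φ((m + 6.4 − 10)/10).

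| m | Sham | GAE | Fisher power, 44 per arm (exact) |
|---|---|---|---|
| 0 | 16% | 36% | 48% |
| 5 | 31% | 56% | 56% |
| 10 | 50% | 74% | 56% |

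For m = 2 and 8, exact power is 54% and 56%. Simulated values for m from 2 to 8 scatter over about 52-59%. The exact true size of Fisher's test over these response rates is 2.5-2.9%.

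**3. Adding the baseline score.** The correlation ρ between baseline and 6-month score is also not in the document. With equal SDs, the correlation of baseline with change is −√((1 − ρ)/2), for example −0.5 at ρ = 0.5. Simulated power (2,000 replicates, 44 per arm, m = 5, SD of change 10):

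| ρ | Fisher | Unadjusted logistic | Baseline-adjusted logistic | Total gain | From leaving Fisher | From covariate |
|---|---|---|---|---|---|---|
| 0.3 | 57% | 65% | 76% | 19 | 8 | 11 |
| 0.5 | 58% | 66% | 73% | 15 | 8 | 7 |
| 0.7 | 56% | 64% | 69% | 13 | 8 | 5 |
| 0.8 | 54% | 62% | 65% | 11 | 8 | 3 |

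Over m from 2 to 8 and ρ from 0.3 to 0.8, the total gain is about 11-20 points: about 7-10 from leaving Fisher's test and about 3-13 from the covariate.

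**4. The other reading of the SD.** If 10 is the SD of the scores, the SD of change is 10 × √(2 − 2ρ). Simulated power at 44 per arm, m = 5 (2,500 replicates):

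| ρ | SD of change | Fisher | Unadjusted logistic | Adjusted logistic | Total gain |
|---|---|---|---|---|---|
| 0.3 | 11.83 | 42.4% | 53.0% | 65.2% | 22.8 |
| 0.5 | 10.00 | 54.4% | 63.7% | 73.5% | 19.1 |
| 0.7 | 7.75 | 80.9% | 86.7% | 89.7% | 8.8 |
| 0.8 | 6.32 | 92.6% | 95.4% | 96.3% | 3.7 |

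At ρ = 0.8 over a wider grid (m from 0 to 10, 44 or 55 per arm), the total gain is about 2-11 points and the covariate alone adds at most about 2.

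**5. Error rate.** Under no effect, Fisher's test rejected in about 2-4% of simulated trials and the adjusted model in about 3.5-6% (simulation error about 0.5 points). The gain comes mainly from using the nominal 5% and from the covariate, not from a materially inflated error rate.

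**The case against.** **What stands.**
- Fisher's test controls type I error, and chance baseline imbalance is already covered by that error rate. A reader might infer that the unadjusted comparison is biased or invalid; under randomisation it is neither.
- A reader might infer that the trial falls short of its stated power. The 85% is claimed for KOOS4 only, and that analysis is baseline-adjusted.
- A reader might put the whole gain down to ignoring baseline KOOS. About half of the central gain comes from Fisher's conservatism, and an unadjusted chi-square test would recover that part.
- A reader might take it that all the ANCOVAs adjust for baseline KOOS. The VAS model uses baseline pain.
- The Fisher sentence names the subscales, but the power figures use KOOS4 inputs. The document gives no effect or SD for any subscale, so the figures do not carry over to them.
- The correlation and the sham response are assumptions.
- Nobody scoring above 90 can gain 10 points on a 0-100 scale, but entry requires VAS of at least 50, so such scores should be rare. The simulations include no ceiling.
- Adjustment would not remove every disagreement with the primary: even adjusted, central power is about 73% against 85%, because dichotomising loses information.

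**What does not stand.** One could say that the continuous ANCOVAs already give the efficient analysis and that the proportion is only a simple clinical reading. The article nevertheless places clinical success among the outcomes with hypothesis testing, so the efficiency of its test matters. Nor is this a detail left to an unseen analysis plan: the method is stated.

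**Conclusion.** The point holds as a loss of efficiency on a secondary outcome. It is not an error of validity, and the primary analysis is unaffected. With SD 10 as the SD of change, a sham mean change of 2 to 8 and a correlation of 0.3 to 0.8, the gain from replacing Fisher's test by baseline-adjusted logistic regression is about 11-20 points, from a Fisher power of about 52-59%. The covariate accounts for about 3-13 of these points and Fisher's conservatism for about 7-10. With SD 10 as the SD of the scores and a correlation of 0.8, the gain can shrink to about 3-5 points (2-11 over the wider grid), from a Fisher power that is then already high in most scenarios. The documents do not settle which case applies. There is also a gap in wording: the only named test for responder proportions is attached to outcomes listed as descriptive, and the hypothesis-tested outcome has no test of its own.

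**What to change.** In the Endpoints part of the Statistics section:

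1. Name the test for the hypothesis-tested clinical-success outcome explicitly.
2. Analyse it, and any subscale responder comparison that is tested, by logistic regression on treatment arm and the matching baseline KOOS score (baseline KOOS4 if success is defined on KOOS4, the baseline subscale score for a subscale).
3. Report the baseline-standardised difference in responder proportions with a 95% CI.
4. Keep Fisher's exact test as a sensitivity analysis, which also covers sparse cells or non-convergence.

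This takes a sentence or two and needs no new data, visits or participants. Logistic regression is already foreseen as the fallback for VAS. The cost is some model dependence and a standardisation step. The change should be made before unblinded data are analysed, since a later switch would look data-driven.
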